## Abstract

**Background:**

Social prescribing is a mechanism for connecting patients with non-medical forms of support within the community and has been shown to improve loneliness. Yet uptake from young people (YP) has been lower than for adults. That is thought to be the case because young people are less likely to engage with primary care for wellbeing support, where social prescribing is based. The INACT study will pilot a social prescribing pathway via schools to support young people who are lonely, testing its feasibility and acceptability of delivering, and evaluating its impact on loneliness through a randomised controlled trial.

**Methods:**

This pilot study utilises a two-group (intervention vs. active control) parallel randomised design, with YP as the unit of randomisation. Approximately 78 pupils reporting loneliness will be recruited across 12 mainstream (6 primary and 6 secondary) schools in England. The co-produced social prescribing intervention includes 6-12 sessions over an 8-week period with a Link Worker who will work with individuals, on a one-to-one basis, to understand ‘what matters to them’ and connect them with local sources of support. Pupils in the control group will receive signposting to sources of support from school staff. Data will be collected at baseline, 3- and 6-month follow-up. Acceptability and feasibility will be assessed via participant recruitment and retention, and via qualitative interviews. Interviews will also explore barriers and facilitators to engagement and implementation and mechanisms of change. Primary and secondary outcomes will be completed to assess response and completeness, including measures of loneliness, mental health and wellbeing.

**Discussion:**

The INACT study will provide preliminary evidence of the feasibility and acceptability of both the research design and social prescribing intervention. Results will inform a planned future randomised trial.

**Trial registration:**

ClinicalTrials.gov NCT06656663.

## Introduction

The transition from childhood to adolescence (with adolescence comprising the period between 10–24 years of age) is a critical development period, with major physical, psychological, and social changes occurring [1]. During this time, social connections, including friendships, are known to be cornerstones of healthy adolescent development [2]. Without social and community connections, negative impacts can occur [2], including loneliness, which in turn triggers negative cycles of psychophysiological symptoms [3]. Loneliness is longitudinally associated with depression symptoms from childhood to adolescence [4] and can result in physical manifestations, such as poor sleep, changes to appetite, and headaches [5,6]. Young people (YP) who report loneliness are also at increased risk of cardiovascular disease and psychiatric disorders in adulthood [7,8]. It is theorised that prolonged loneliness adversely affects health via multiple mechanisms, including the dysregulation of physiological systems involved in social connections [9].

Data from the UK show that YP report some of the highest prevalence rates of loneliness across different age groups, with 11.3% of YP aged 10-15 years old stating they always or often feel lonely [10]. This is not distributed equally, with higher levels of loneliness reported amongst younger individuals (14%), those who live in cities (19.5%) and those who receive free school meals (27.5%) [10]. In the last 30 years, data from international samples of YP suggests that levels of loneliness have been increasing, with marked rates of growth occurring from the late 1990’s onwards [11,12]. The Covid-19 pandemic further exacerbated feelings of loneliness, with 35% of YP reporting often feeling lonely during lockdowns [13].

A recent review and meta-analysis of interventions that tackle loneliness in YP demonstrated a moderate effect size overall [14]. However, most interventions targeted YP *at risk of loneliness* (e.g., due to physical health difficulties), rather than those *who reported lonelines*s. Effect sizes did not significantly differ based on intervention characteristics. However, the authors noted that a ‘one-size fits all’ approach is unlikely to reduce loneliness among YP, and that a tailored approach based on individual needs should be considered in future interventions. The authors of the review also noted evidence gaps including the lack of longer-term follow-up and targeted interventions for YP reporting loneliness, and the need to consider socioeconomic and other risk factors for targeted interventions [14].

Social prescribing (SP) is a mechanism of care aimed to address health inequalities by linking patients with non-medical forms of existing support within their local communities [15]. It usually involves a health or social care professional referring a patient to a Link Worker (LW), who co-develops a non-clinical plan with the patient based on their values, needs and preferences and connects them with existing community organisations to improve health, wellbeing or other aspects of the patient’s life [16]. Community support can include (but is not limited to) the arts, music, access to nature, volunteering, gardening, exercise, and broader support services [15]. The future priorities of the UK’s ‘Campaign to End Loneliness’ firmly support the need for SP services, highlighting the need for ‘connector services that reach, understand, and support lonely individuals’ to ‘increase connections, improve relationships and change an individual’s thinking’ [17]. These services can be delivered via psychological methods, one-to-one support, and group support. SP incorporates elements of all three [18].

Recent reviews into the impact of SP on loneliness suggest that SP can have a positive impact [19] and that both participants and service providers believe it to be helpful [20]. However, those studies were limited to adult populations and often lacked control groups [20]. When control groups are utilised, results suggest that SP is beneficial [21,22]. In one UK study on SP for adults who reported loneliness, 37% of those who received SP were classified as ‘not lonely’ at 3-month follow-up, compared to 20% of those in the matched control group [22]. There was also evidence to suggest that younger age groups (those ages 18-50 years old) benefitted more than older adults [22]. Similarly, a controlled trial in Australia exploring the impact of SP on 114 adults showed that 8 weeks after starting SP, the intervention group reported decreased loneliness with a large effect size [21]. Retention of those allocated to SP was also high at 79.4% [21]. Whilst the evidence for youth SP is less developed, a recent review found that SP is a promising way of tackling loneliness among YP, although there are methodological concerns, including the small number of participants, meaning robust conclusions could not be drawn [23]. Accordingly, there is a critical need for robust research that can provide insight into SP for YP who report loneliness.

SP is supposed to be an ‘all age’ model [24], yet research suggests that uptake from YP remains lower than for adults [25]. While YP see the benefits of SP [26], the dominant model of delivery through family doctors in the UK may be inhibiting youth involvement as they do not feel comfortable accessing wellbeing support in this way [27]. Schools may be better placed to deliver wellbeing initiatives and targeted interventions for loneliness, as they serve as a universal point of access for YP [28]. Schools could act as a conduit to connect YP to community support and have started to be used as a venue to facilitate SP in the UK [29]. The building blocks for SP are already in place, with the rollout of specialist youth LWs across England and an increasing number of community organisations delivering activities suitable for youth SP. However, SP has not yet been properly embedded into schools, and educational stakeholders have been underrepresented in SP pathway development. More work needs to be undertaken to ensure adequate information sharing between agencies, such as schools and LWs [29]. To date, no studies have explored SP in school settings.

Given the high rates of loneliness among YP and the lack of interventions targeting loneliness in this cohort [14], this proposed study will focus on piloting a novel SP pathway in schools for pupils reporting low community connection or loneliness. The aims of this pilot study are to ensure the following:

i)The SP pathway and study design are feasible, acceptable and suitable;ii)The proposed measurement framework is tested for feasibility, acceptability and suitability, andiii)Quantitative data are collected to inform a better estimation of the required sample size for a full trial.

### Research questions (RQs)

***(RQi)*** Is the SP pathway for youth reporting low community connection or loneliness feasible, acceptable and suitable to stakeholders?

***(RQii)*** Is the study design, including measurement framework, feasible, acceptable and suitable to stakeholders?

***(RQiii)*** Are the assumptions in the power calculation (specifically the intraclass correlation coefficients) realistic to allow for adequate power to be able to test for differences?

## Materials and methods

### Design

This manuscript relates to the INACT pilot study protocol V1.0 05-02-24 and follows the SPIRIT checklist (see S1 Checklist). Any details of protocol amendments will be submitted to the journal after approval from UCL ethics committee. INACT will adopt a two-group (intervention vs. active control) parallel randomised design, with YP as the unit of randomisation. YP allocated to the intervention arm will receive SP, while those in the control arm will receive signposting from school staff to activities in their local area. Outcomes will be assessed at baseline (T0), 3 months after being allocated to SP or signposting (T1), and 6 months after being allocated to SP or signposting (T2).

### Setting

This study will involve primary and secondary schools in England. We aim to recruit our sample from mainstream schools across 3 cities: London, Leeds, and Manchester. These sites have been selected due to their (i) urbanicity, (ii) diversity in socio-economic status, and (iii) high levels of deprivation, which are known to affect community connection and loneliness [10].

### Participants

We aim to recruit a total of 12 schools (6 primary schools and 6 secondary schools). In each primary school, one class from each of Years 4 and 5 (children aged 9 and 10 years old) will be selected, whilst in secondary schools, two classes each from Years 7 and 8 (children aged 12 and 13 years old) will be selected. Year 6 (children aged 11 years old) will be excluded from taking part because previous studies by the research team have shown that schools are reluctant to engage Year 6 students in research due to exam preparation [30,31]. Private schools will be excluded because they have greater resource to support YP with wellbeing difficulties and do not use unique pupil numbers linked to the National Pupil Database, which will be needed to explore factors associated with low community connection and loneliness.

Approximately 780 pupils (exact number dependant on class size) will complete baseline surveys to examine the prevalence rates of low community connection and loneliness and factors that predict this. Under realistic assumptions from other trials [31] and reviews on low community connection and loneliness [14] (low community connection/loneliness prevalence =  14%, participation rate =  71%), approximately 78 pupils will participate in the pilot study (39 receiving SP and 39 receiving signposting). YP eligible for the pilot study will be those reporting feelings of loneliness (≥6) using the 3 loneliness questions from the Good Childhood Index [32]. This corresponds to YP who report feeling lonely at least some of the time across all three questions. YP who are persistently absent from school will be included. YP reporting severe learning disability will be excluded.

In addition to YP, approximately 20 other stakeholders, namely LWs and school pastoral staff, will participate in the pilot study. Pre-intervention, a single member of staff in each participating school will be asked to complete a school wellbeing provision survey. Typically, this will be the named mental health lead; in schools where there is no named mental health lead, it may be the member of staff with primary responsibility for personal, social and health education (PSHE) provision or pastoral support. Post-intervention, school staff who were involved in signposting and LWs who provided SP will be asked to complete a feasibility, acceptability and suitability survey.

Finally, a subsample of YP (n =  24) and stakeholders (n =  18) in the intervention arm will be asked to take part in a qualitative interview to better understand the feasibility and acceptability of the SP pathway, as well as barriers and facilitators to engagement and implementation. Topic guides are shown in the S1 and S2 Files. Purposive sampling will be employed. For YP, purposive sampling will take into account socio-demographic factors, such as age, gender, ethnicity, site, loneliness score, and the degree to which they engaged in SP (none, some, a lot). For LWs and school staff, purposive sampling will take into account sociodemographic factors, location, role, and types of activities prescribed (for LWs). The number of interviews has been selected to be large enough to allow for adequate “information power” and to make meaningful comparisons between social prescribing pathway delivery and experiences in different sites [33] but not too large to dilute an in-depth rich analysis and exploration of individual participant accounts.

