### Procedure

Our recruitment strategy will include (i) drawing on established school networks (e.g., the Schools in Mind network, containing over 30,000 schools), (ii) undertaking an extensive targeted social media campaign towards educational professionals in cities of interest; (iii) attending headteacher network meetings to promote the project; (iv) purchasing the Sprint education database, which contains up-to-date contact details on 570,000 teachers and senior staff at UK schools, (v) offering transparent and accessible communication regarding what school participation entails formalised in a Memorandum of Understanding (MOU), and (vi) compensation of £500 per school for administrative support.

Schools will be recruited by the methods specified above, beginning 01/03/24 and ending 30/06/24 with the aim of starting the pilot interventions on 03/01/25. Schools that express an interest will be asked to fill out a MOU agreeing to participate. As interest is likely to exceed capacity during the pilot, schools will be held in reserve (in case of drop out) or for participation in the full trial. Following recruitment of schools, YP in relevant year groups will be recruited in two stages. Firstly, schools will send letters to parents/carers of pupils in selected classes, including to those identified as persistently absent. The letter will be sent between 16/09/24-31/10/24 and provide information about the study and allow parents/carers to opt their children out of the study. Secondly, for parents and guardians that do not opt out their YP, the YP must assent by reading through an online information sheet and completing an online consent form before they can take part in the baseline survey. Data collection for baseline surveys and YP assent will start on 12/11/24 and be completed by 30/11/24 in all schools. Thus, participant recruitment will be completed by 30/11/24. Follow up data collection will be completed by 01/07/25 and the study completion date is the 31/08/25. For the qualitative interviews, separate information sheets and opt-in consent forms will be provided to parents/carers and YP who are interested in participating.

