To identify eligible YP, baseline surveys will be administered to classes of pupils in relevant year groups during PSHE (or another appropriate lesson determined by the school). For pupils who are persistently absent from school, baseline surveys can be completed in their own time (e.g. at home), or with researchers or school pastoral staff at pupils’ convenience. Those who meet the inclusion criteria will then be randomly allocated to receive SP (the intervention) or signposting (the active control). Random allocation will be undertaken by a statistician at the pupil level, stratifying for location. Given the nature of the intervention blinding of participants or researchers is not possible. As LWs will only be able to work with individuals allocated to the intervention arm, this will prevent contamination effects, and all pupils will have access to the same list of community resources. Those allocated to SP will then be contacted by a LW who will arrange a time to meet with them. For those allocated to signposting, researchers will share the names of YP with school pastoral staff who will signpost them to community resources. Any YP identified as having significant mental health issues on the Me & My Feelings questionnaire [34] will be highlighted to pastoral staff regardless of intervention group.

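### The 71% participation rate is applied to 780 pupils already counted as baseline completers, so the flow as written randomises about 109 pupils, not 78

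*Protocol article*

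**What the plan says.** The Participants section gives the whole sample-size chain. It starts from the survey: "Approximately 780 pupils (exact number dependant on class size) will complete baseline surveys". It then states its planning assumptions ("low community connection/loneliness prevalence = 14%, participation rate = 71", the last figure also a percentage) and ends with "approximately 78 pupils will participate in the pilot study (39 receiving SP and 39 receiving signposting"). The Methods part of the abstract describes the same number as recruited: "Approximately 78 pupils reporting loneliness will be recruited across 12 mainstream (6 primary and 6 secondary) schools in England".

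The Procedure section gives the order of events. Letters go to parents, who may opt their child out. Pupils who are not opted out must assent by "completing an online consent form before they can take part in the baseline survey". The survey window closes on 30 November 2024, and the section concludes: "Thus, participant recruitment will be completed by 30/11/24". After that, "Those who meet the inclusion criteria will then be randomly allocated to receive SP (the intervention) or signposting (the active control"). No second consent or agreement step between survey and allocation is described. Pupils who decline what they are allocated may still complete follow-up questionnaires, for the intention-to-treat analysis.

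**The concern.** A participation rate belongs at the step where pupils can decline to take part. In the written sequence, parents and pupils make that choice before the baseline survey. A pupil counted as completing the survey has already passed it, yet the 71% is taken off again after the survey to reach 78.

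This matters because the article is a feasibility pilot, and the flow of pupils is part of what it tests. The stop-go criteria in Table 1 (Data analysis section) include the proportion completing baseline and the proportion attending a link worker appointment. Both need a clear denominator, and the article leaves open whether 780 is the number approached or the number completing, and whether the intervention arm is 39 pupils or about 55.

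**Working it through.** **Inputs**

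- 780 pupils completing baseline; prevalence 14%; participation 71%; 78 participants, 39 per arm (all from Participants).
- 78 described as recruited (abstract, Methods).
- Order of steps: opt-out, assent, survey, end of recruitment, randomisation (Procedure).
- Classes: 6 primary schools with 2 classes each and 6 secondary schools with 4 classes each (Participants).

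**1. Reproduce the plan's figure.** 780 x 0.14 = 109.2, and 109.2 x 0.71 = 77.5, which rounds to 78. Without the 71% the result is 109, so the plan's figure needs both factors.

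**2. Follow the written sequence.** If 780 complete the survey, opt-out and assent are already behind them. The eligible pupils number 780 x 0.14 = 109.2, and these are randomised: 109.2 / 2 = 54.6, or 54-55 per arm. The ratio to the stated size is 109.2 / 78 = 1.40.

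**3. Compare the readings of the 71%.**

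| Reading | Invited | Completing baseline | Randomised | Conflicts with |
|---|---|---|---|---|
| 780 complete; 71% acts before the survey | 780 / 0.71 = 1,099 | 780 | 109 (54-55 per arm) | 78 in Participants and abstract |
| 780 are invited; 71% acts before the survey | 780 | 780 x 0.71 = 554 | 554 x 0.14 = 78 (39 per arm) | 780 as survey completers |
| 780 complete; 71% is uptake after allocation | not stated | 780 | 109 (54-55 per arm), of whom 109.2 x 0.71 = 78 receive their allocation | 78 recruited in the abstract |

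Each reading contradicts a stated figure or the description attached to it.

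**4. Class count.** There are 6 x 2 + 6 x 4 = 36 classes. If 780 are invited, the average is 780 / 36 = 21.7 pupils per class. If 780 complete after 71% participation, it is 1,099 / 36 = 30.5. The article gives no class size, so this does not settle the matter. It does show that the two readings describe materially different designs.

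**5. Effect on the stop-go criteria.** Full marks for link worker attendance start at 55%.

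- With 39 allocated: 0.55 x 39 = 21.45, so 22 attenders.
- With 54 or 55 allocated: 0.55 x 54 = 29.7 and 0.55 x 55 = 30.25, so 30 or 31 attenders.

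For baseline completion, the expected proportion is 71% if the rate acts before the survey (554 / 780 or 780 / 1,099). If the 71% is uptake, the article gives no expected baseline completion at all.

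**The case against.** The best defence is that a step does exist after the survey. The Procedure section provides for pupils who turn down their allocation, the section on implementation measures counts those who take up social prescribing once offered, and Participants speaks of pupils receiving each arm. Read that way, 780 complete, 109 are eligible and 78 receive what they were allocated. This stands to the extent that 780 and 78 are not strictly irreconcilable. It does not rescue the stated trial size. About 109 would still be randomised, a number the article gives nowhere. Those who decline can still complete follow-up for intention-to-treat. Recruitment is not the same as taking up an offer. The reading also needs the same 71% uptake for link worker sessions and for a leaflet from school staff.

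It is also fair to say that the counts are approximate, that no power claim rests on 78, and that the source of the 71% is not shown. A 40% difference is more than rounding, however. If the full protocol contains an agreement step between survey and randomisation, the article as written contradicts it by closing recruitment with the survey.

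A reader might go further and infer that 152 or more pupils would be randomised, since the Introduction reports "those who live in cities (19.5%) and those who receive free school meals (27.5" (the second figure also a percentage): 780 x 0.195 = 152 and 780 x 0.275 = 215. The documents do not support this. Those are background figures, apparently for feeling lonely always or often, whereas eligibility is a total of at least 6 on three items, for which no prevalence is given. Applying 27.5% to everyone would treat all pupils as receiving free school meals. The planning 14% is credited to other sources, so its match with a 14% in the Introduction proves nothing. At most these are sensitivity scenarios.

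A reader might also infer that link workers would be overloaded or that a sampling cap is needed. Link worker capacity is never stated, so neither follows.

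**Conclusion.** The stated sample size is wrong as written. With 780 baseline completers, the plan's own 14% and the sequence in the Procedure section, about 109 pupils are randomised (54-55 per arm), not 78 (39 per arm). Conversely, 78 randomised corresponds to about 554 completers out of 780 invited. The result rests on two things: the 14% being taken as given, and the article's account of the flow being complete, with no consent step between survey and allocation. Treating the 71% as post-allocation uptake changes what 78 means but leaves about 109 randomised. The finding concerns the consistency of the stated numbers. It does not show that 14% is too low or that delivery capacity would be exceeded.

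**What to change.** Make three linked changes in Participants, and carry them into the abstract and Table 1:

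- State whether 780 is the number of pupils invited or the number completing baseline.
- Name the single step to which the 71% applies, and apply it once.
- Restate the expected number randomised and per arm to match: about 109 (54-55 per arm) if 780 complete; or about 554 completing and about 78 randomised (39 per arm) if 780 are invited. If the 71% is meant as uptake, give about 109 as randomised and label 78 as the number receiving their allocation.

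Then use the same denominators for the baseline-completion and link-worker-attendance stop-go criteria. The cost is a few restated figures and one or two sentences. No extra pupils and no change of design are needed.
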